### Demographic surveillance

During successive rounds of health and demographic surveillance (see Figs. 1 and 2 for schedules), records of the complete population of the island were maintained by door-to-door visits, collecting data using a tablet computer installed with data collection and management software (see the section on data entry and management below) [34]. Data were uploaded to the local server on a daily basis, creating a near real-time demographic database that subsequently served other parts of the project. A team of fieldworkers collected data simultaneously in all nine metaclusters on a daily basis. Over the course of 3 months all households and individuals were visited by fieldworkers to update demographic information. By conducting successive rounds of surveillance, data were available for each of the 81 clusters throughout the baseline and rollout period, thus providing information about both arms of the intervention for before-and-after and contemporaneous measures of intervention effect. The last survey before the start of the intervention rollout served as a baseline record of the population, and took place from January to June 2013. The location of all houses was recorded using a GPS built into the tablet computers.

### Measurement of malaria incidence and prevalence

Clinical malaria incidence was recorded during the routine HDSS surveillance of all individuals (three rounds of surveillance each year, see Figs. 1 and 2). During household visits residents were asked to report any fever in the previous 2 weeks, 2 days and at the time of the visit. If fever was reported to have occurred within 2 weeks of the visit, body temperature was measured using an in-ear thermometer (Braun™ IRT 3020). If the measured in-ear temperature was greater than 37.4 °C, the individual was tested for malaria using an RDT (*SD BIOLINE*™ Malaria Ag P.f/Pan *HRP*-*II*/pLDH). Any person with a positive RDT was provided with an appropriate dose of artemether-lumefantrine or referred to a local health clinic in the case of pregnancy, child under 6 months of age or severe symptoms. By collecting clinical malaria data continuously, information was available for baseline and throughout the course of the rollout for all 81 of the clusters.

In addition to the detection of malaria-associated fever within the HDSS, cross-sectional malaria prevalence surveys were carried out in a randomly selected 10 % of the study population three times per year (Figs. 1 and 2). All selected individuals were tested for malaria using an RDT, and a dry blood spot was also collected from each person as well as a measure of in-ear temperature. Validation of RDTs was performed using high-resolution melting PCR (HRM-PCR) [35] on a random sample of 200 dry blood spots from each round of surveillance. As for the HDSS and clinical malaria monitoring process, this data collection method allowed for measurement of malaria prevalence in all 81 clusters of the SWCRT at regular intervals throughout the course of the project.

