### Study objectives

#### Primary objective

The primary objective is to measure the effect of mass mosquito trapping on clinical malaria incidence, measured as fever plus positive rapid diagnostic test (RDT) result.

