**Fig. 3 Fig3:**
[figure not shown]
Rusinga Island with 81 project clusters, each containing 50–51 households, numbered consecutively in the order in which the SMoTS were installed. Metaclusters, each containing nine clusters, are outlined in *bold red lines*. Insets show close-up views of geographically smaller clusters in the northwest and southeast of the island. The blank space at the centre of the island is an uninhabited hill

Computer simulations of possible rollout scenarios were made on the basis of a human susceptible-infected-susceptible transmission model [33]. A hierarchical design was selected and adopted as the rollout strategy for SolarMal. The design groups the 81 clusters of 50 or 51 households into nine larger areas, each referred to as a metacluster. Within every metacluster the intervention was subsequently introduced to each of nine clusters in a random order. Once the intervention had been applied to all clusters in one metacluster, the rollout moved randomly to the next metacluster; all clusters eventually received the intervention according to this SWCRT design. The nature of the intervention (visible trap outside the house and solar panel on the roof) meant that it was not possible to blind the intervention.

Prior to a community rollout ballot held in May 2013, a large number of possible rollout sequences were computer generated, each consisting of a distinct ordering of the 81 clusters [33]. Nine possible rollout sequences (each of which was compliant with statistical power calculations and requirements of the community) were presented by the researchers for blind selection by community members, with one sequence starting in each of the nine metaclusters and preserving independence among metaclusters. After placing a printed map of each sequence in a sealed, unmarked envelope and placing the nine envelopes into a box, one member of the community was chosen at random to draw an envelope and open it to reveal the order of the rollout which would be followed [24]. The selected SWCRT sequence is illustrated in Fig. 3.

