### Analytical plan

The datasets included for the analysis comprise results of the HDSS, clinical malaria surveys, cross-sectional malaria prevalence surveys and monitoring of mosquito densities. Malaria fever incidence is the primary outcome of the trial. Data are included up to the end of the next month after full intervention coverage was attained. For analyses of parasitological as well as entomological outcomes, intervention status is classified week by week on the basis of whether traps had been installed in the cluster. The whole study cluster is classified as intervened or non-intervened based on whether installation was complete in that cluster by the end of the week. Clusters are excluded from analysis during weeks in which some, but not all, of the households were provided with the intervention (i.e. during the week in which installations took place in that cluster). For malaria prevalence and incidence, the numbers and proportions of positive RDT tests were summarised by week and arm of the trial. For mosquito densities, rates of anophelines collected per trapping night were presented by week and arm of the trial.

Following the SWCRT design described by Silkey et al. [33], an analytical plan was constructed. The primary analysis of the impact of the trial on clinical malaria incidence, prevalence and vector densities follows two measures of effect: a contemporaneous comparison comparing the outcomes in intervened clusters with the not yet intervened clusters and a comparison of the final results in intervened areas with the baseline status. Generalized linear mixed models (GLMMs) with a binomial distribution will be deployed to carry out significance testing against the null hypothesis of no effect using a likelihood ratio test. For mosquito densities a GLMM will be used with a Poisson distribution. For analysis of medical and entomological data, random effects will be used to allow for spatial effects (cluster) as well as effects of round of surveillance (time period within cluster). Final models will consider possible confounding effects on the relationship between the intervention effect and measured outcomes. The analytical plan did not include any interim analyses.

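### Because an HDSS resident is measured only after reporting fever, a change in reporting after unblinded trap installation would bias the primary clinical-malaria contrast in either direction

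*Protocol article*

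**What the plan says.** The primary objective concerns clinical malaria incidence, "measured as fever plus positive rapid diagnostic test (RDT) result", and the Analytical plan confirms: "Malaria fever incidence is the primary outcome of the trial".

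The section on measuring incidence and prevalence sets out a chain of three steps for the HDSS:

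1. "During household visits residents were asked to report any fever in the previous 2 weeks, 2 days and at the time of the visit".
2. "If fever was reported to have occurred within 2 weeks of the visit, body temperature was measured using an in-ear thermometer".
3. "If the measured in-ear temperature was greater than 37.4" °C, an RDT is done.

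The section on randomising the allocation states that, with a visible trap and solar panel, "it was not possible to blind the intervention".

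The same measurement section describes a second data source. Three times a year a random 10 % of the population is surveyed. Everyone selected has an RDT and a dried blood spot, "as well as a measure of in-ear temperature", with no condition on reported fever.

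The Analytical plan applies two contrasts to clinical incidence, prevalence and vector density alike: intervened against not-yet-intervened clusters, and final results against baseline. The secondary objectives include all-cause fever, both as measured and as reported, without naming the data source.

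**The concern.** The case definition looks objective because it ends in a thermometer reading and an RDT. Entry to both, however, rests on what a resident tells a project fieldworker, and both can see whether the house has a trap.

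Installation also changes contact with the project. Residents are invited to a workshop on malaria two weeks beforehand. Intervened households then have their baits replaced by project staff every three months, and they gain light and phone charging. Any of these could move the willingness to report fever, up or down.

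The thermometer and RDT stop a false report from becoming a case. They cannot recover a true case that was not reported. The bias therefore runs entirely through missed cases. Neither contrast removes it, because reporting could differ both between clusters at one time and between baseline and the end. Repeated visits would narrow the interval around the biased value without moving it.

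**Working it through.** **Bias identity.** Let p0 and p1 be the true probabilities per visit that a resident is above 37.4 °C and RDT-positive, without and with traps. Let s0 and s1 be the probabilities that such a resident reports fever. Only reported cases are counted, so

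apparent rate ratio = (p1 × s1) / (p0 × s0) = true rate ratio × s1/s0.

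If everyone were measured whatever they reported, s1/s0 would be 1.

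**The plan's own figure.** The section on power gives 80 % power for about a 52 % reduction with an effective sample of 7914. It states no baseline incidence, alpha or sidedness, so the figure cannot be reproduced independently. It can be solved backwards. With two-sided alpha 0.05 and 3957 per arm (both assumed), the comparison of two proportions gives a control rate of about 1.08 % per visit. If 7914 were per arm, the rate would be 0.54 %. The 1.08 % is used below as an assumption.

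**Size if traps have no effect.** The documents give no reporting rates, so s1/s0 is assumed. The last column uses one visit per person, 3957 per arm and a 1.08 % control rate. The nominal value in that direction is 2.5 %.

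| s1/s0 | Spurious fall (1 − s1/s0) | Chance of a significant spurious fall |
|---|---|---|
| 0.95 | 5 % | 4 % |
| 0.90 | 10 % | 7 % |
| 0.80 | 20 % | 16 % |

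**The opposite direction.** If traps truly gave a rate ratio of 0.48 and reporting rose from 80 % to 90 % (assumed), then s1/s0 = 0.90/0.80 = 1.125. The apparent ratio would be 0.48 × 1.125 = 0.54, so a 52 % reduction would appear as 46 %.

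**What the surveys can show.** Six surveys are assumed, as in the section on power, with an even split by intervention status and no clustering. The standard error of the log rate ratio is √(1/d0 + 1/d1), where d0 and d1 are the case counts.

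- *Full 10 % sample.* 6 × 0.10 × 23,337 = 14,002 records, against 6 × 23,337 = 140,022 HDSS visits. Control cases: 7,001 × 0.0108 ≈ 76. Intervened cases at ratio 0.48: about 36. The standard error is √(1/76 + 1/36) ≈ 0.202, and the 95 % interval is about 0.32 to 0.71.
- *The plan's minimum of 907 per survey.* 6 × 907 = 5,442 records, giving about 29.4 and 14.1 cases. The standard error is about 0.324, and the interval is about 0.25 to 0.91.
- *A smaller effect, ratio 0.80, full sample.* About 75.6 and 60.5 cases. The standard error is about 0.173, and the interval is about 0.57 to 1.12.

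Clustering and adjustment for time would widen all three.

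**The case against.** The strongest reply is that the plan already holds outcomes that do not pass through reported fever. RDT prevalence and vector density are analysed with the same contrasts, and the Discussion says that human-health and entomological outcomes will be read together to attribute an effect. A reader might infer that nothing in the trial could expose a reporting artefact. The documents do not support that: a fall in clinical cases with flat prevalence and flat mosquito counts would look suspect. RDT prevalence, at 23.7 % at baseline, is also the more precise check. What remains is that prevalence counts all infections and density counts mosquitoes. Neither measures febrile malaria.

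Second, the secondary objectives already compare reported and measured fever between intervened and non-intervened areas, which covers part of the remedy. A reader might infer that measured fever comes from the HDSS and shares the reporting step. The text does not say so, and the surveys could supply it. The source needs to be stated.

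Third, the bias needs someone febrile at the visit and infected who denies fever now and over the past two weeks. Treatment is available to RDT-positive residents in both arms, which encourages reporting. This may dampen the effect but does not exclude it.

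Fourth, supporting analyses often belong in a SAP, which is not shown. Their absence from an article is therefore not the point. The point is the measurement rule that the article itself fixes.

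**Conclusion.** The concern holds as a structural risk of unknown size and unknown direction. Reported fever decides who is measured for the primary outcome of an unblinded trial, and neither planned contrast removes a change in reporting.

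A reader might go further and conclude that a positive result would be a reporting artefact. The documents do not support this. They contain no data on reporting, and the 5 % to 20 % range rests wholly on assumed ratios of 0.95 to 0.80. To produce the planned 52 % reduction from reporting alone, s1/s0 would have to be 0.48, meaning that reporting among true cases fell by about half. Increased reporting would hide a benefit instead.

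The intervals for the survey check rest on the back-calculated 1.08 % control rate, six surveys, an even split and no clustering. On those terms the check is informative near the planned effect and weak for small ones.

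**What to change.** Unless the SAP already contains it, prespecify a supporting analysis of the primary objective:

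- Apply the same case definition (in-ear temperature above 37.4 °C and positive RDT) to everyone in the 10 % surveys, whatever fever they report. Use all surveyed persons as denominator, with the contrasts and model of the primary analysis.
- Report the estimate with its confidence interval beside the HDSS estimate and RDT prevalence.
- State that measured all-cause fever in the secondary objectives is taken from these surveys.
- Report by intervention status the share of HDSS visits with any reported fever, and the share of those confirmed by thermometer.

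Do not make the trial's conclusion depend on the two estimates pointing the same way. With no true effect, an unbiased survey estimate would favour the traps about half the time, so such a rule would pass about half of pure reporting artefacts.

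The cost is one extra analysis and a short table on data already collected. The drawback is low precision, since the surveys hold about one tenth of the HDSS records or fewer.

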In this rural region of Kenya, few residential buildings are connected to the main electrical grid, and most households light their homes using kerosene tin lamps. The requirement of electrical energy to power the fan inside the odour-baited trap prompted the decision to integrate the mosquito trapping systems into a solar-home system, henceforth referred to as a solar-powered mosquito trapping system (SMoTS). The SMoTS includes two light emitting diode (LED) lights and a mobile phone charging port in addition to the odour-baited mosquito trap. These additional, immediate, private benefits of the system were expected to increase usability and improve adherence to the public health intervention, which requires the sustained participation of residents [24].

Here we describe the study design and methods used by the SolarMal project to test this intervention on Rusinga Island, western Kenya (the WHO Trial Registration Data Set is given in Additional file 1, and a protocol checklist is given in Additional file 2). The SolarMal project is the first trial to measure the efficacy of this novel approach to malaria vector control. A stepped wedge cluster-randomised approach was applied to the intervention rollout so that the intervention coverage gradually increased from no coverage to coverage of all eligible households over the course of 24 months. During the course of this study we aimed to determine whether the addition of daily removal trapping of malaria mosquitoes to the Kenyan national malaria control strategy (LLINs plus case management) will lead to elimination of malaria from Rusinga Island, western Kenya.

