#### Secondary objectives

The medical objectives are as follows (all outcome measures include contemporaneous comparison of intervened with non-intervened areas, as well as before-and-after measures of intervened areas compared with baseline):To determine the impact of mass mosquito trapping on malaria prevalence measured by RDT, with subsequent high-resolution melting PCR used to estimate the prevalence of sub-patent malariaTo calculate differences in both measured and reported all-cause fevers following the introduction of odour-baited traps

The entomological objectives are as follows (all outcome measures include contemporaneous comparison of intervened with non-intervened areas, as well as before-and-after measures of intervened areas compared with baseline):To assess whether the mass trapping of mosquitoes reduces the population density of malaria vectors on Rusinga IslandTo determine whether the mass distribution of odour-baited mosquito traps leads to changes in mosquito species compositionTo record changes in entomological inoculation rate associated with implementation of the interventionTo compare mosquito densities and species composition indoors and outdoors

The sociological objectives are as follows:To determine the behavioural, socio-cultural and organisational factors that influence the effective and sustainable use of SMoTSTo foster learning relevant to adapting the implementation and sustainability strategy as an integral component of the interventionTo understand how the introduction and use of SMoTS affects and/or is affected by the use of other malaria control interventions

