## Methods/design

### Study area and participant eligibility

The study took place on Rusinga Island, western Kenya, an island that is located approximately 75 km southwest of the city of Kisumu and has a surface area of around 44 km^2^. Research activities are conducted through the Thomas Odhiambo Campus of the International Centre of Insect Physiology and Ecology (*icipe*) in Mbita Point, located 2 km from Rusinga Island. In a population census conducted by the project in May 2012, the total population of the island was 23,337 people, living in 4062 households [25]. The majority of the population belongs to the Luo ethnic group, and Dholuo is the main language spoken by residents. A household (locally referred to as a homestead or *dala*) may comprise more than one house. The primary occupations of people are fishing in Lake Victoria and small-scale farming. The climate is tropical with a long rainy season typically occurring from February to May with a shorter rainy season from October to November. Malaria is typically endemic in this region, and transmission occurs throughout the year [22, 26].

All households and residents of Rusinga Island were eligible for inclusion in the study with recruitment commencing in June 2012 and continuing until November 2015 (Figs. 1 and 2). The assignment of households to clusters and metaclusters (see the section on study design below) was completed in May 2013, and any household constructed before this point was eligible to receive an odour-baited trapping system. Households constructed after this time were eligible to participate in the health and demographic surveillance, parasitological, entomological and sociological studies, but were no longer eligible to receive a SMoTS. As the rollout of SMoTS took two years to complete and we did not return to previously installed project clusters to install SMoTS in new households, limiting SMoTS to those households already built at the start of the rollout meant that the intervention coverage levels were consistent across the island. Had SMoTS been installed in all households (including those built after the start of the rollout) there would have been a greater coverage of SMoTS in those clusters which received the intervention later in the two year rollout process.

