### Power and sample size rationale

There is some controversy about power calculations for SWCRTs [43], and the power of our design depended on the correlation between observations on the same individuals at sequential HDSS visits. We could not determine the level of correlation from the single baseline enumeration visit. A lower bound for the minimum detectable effect size is therefore that of a single visit per person, occurring halfway through the rollout. Using previously published formulae, this approach was anticipated to have had 80 % power to detect approximately 52 % reduction in clinical incidence with an effective sample size of 7914 persons [44]. Analogous calculations for prevalence [44], using a baseline malaria prevalence of 23.7 % (RDT prevalence rate during the baseline survey for this project) and minimum sample size of 907 persons, suggested that a single prevalence survey should have had 80 % power to detect a 27 % reduction in prevalence. Six repeated surveys might have the power to detect effects as small as an 11 % reduction in prevalence, assuming that correlations between repeated observations were small.

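### The PCR sample behind the between-arm comparison of sub-patent malaria is not balanced by arm, so precision is lost that the same 200 tests per round could recover

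*Protocol article*

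**What the plan says.** All places are in the protocol article.

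- *Secondary objectives*: the first medical objective covers RDT prevalence, with "high-resolution melting PCR used to estimate the prevalence of sub-patent" malaria. For the medical objectives, "all outcome measures include contemporaneous comparison of intervened with non-intervened areas", and a comparison with baseline is required as well.
- *Measurement of malaria incidence and prevalence*: each cross-sectional survey covers a "randomly selected 10 % of the study population three times per year", and everyone selected gives both an RDT and a dry blood spot. PCR is then run "on a random sample of 200 dry blood spots from each round of surveillance". The purpose given there is to validate the RDT. No stratification by arm or by RDT result is mentioned.
- *Power and sample size rationale*: the prevalence calculation was made "using a baseline malaria prevalence of 23.7" %. The section deals with clinical incidence and RDT prevalence and gives no power or precision figure for sub-patent infection.
- *Background*: coverage "gradually increased from no coverage to coverage of all eligible households over the course of 24 months".
- *Analytical plan*: mixed models with random effects for cluster and for surveillance round within cluster.

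**The concern.** One PCR sample has to serve two purposes. Checking the RDT needs both RDT-positive and RDT-negative spots. Comparing sub-patent infection between arms needs RDT-negative spots in reasonable number in both arms at the same time. A draw that ignores arm gives each arm a share equal to its current coverage, which is very uneven near the start and end of the rollout.

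The sub-patent comparison helps to show whether a fall in RDT prevalence is a fall in infection or a shift towards infections that the RDT misses. If the contrast is imprecise, that question stays open. Spots are collected from everyone surveyed, so a better-placed 200 could be chosen without more PCR tests.

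**Working it through.** The plan has no precision figure for this outcome, so there is none to reproduce.

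**Inputs from the article.** 200 PCR tests per round; baseline RDT prevalence 23.7%; population 23,337, so about 2,334 spots per round at 10%; 81 clusters; 24-month rollout with three surveys a year, so six rollout rounds.

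**Assumptions.** Linear rollout. The survey calendar is in figures that are not available, so two are tried: (A) months 4, 8, 12, 16, 20 and 23.5; (B) the midpoints of six four-month periods. Sub-patent prevalence is set at 10% of RDT-negative people; without clustering it affects the half-widths but not the ratio of standard errors.

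**Step 1: informative spots.** 200 × (1 − 0.237) ≈ 153 per round; the other 47 are RDT-positive.

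**Step 2: split by arm.** With coverage f, the arms hold 152.6·f and 152.6·(1 − f) RDT-negative spots. The 95% half-width of a single-round difference is 1.96·√(0.1·0.9·(1/n₁ + 1/n₀)).

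| Round | A: intervened/control | A: half-width (points) | B: intervened/control | B: half-width (points) |
|---|---|---|---|---|
| 1 | 25/127 | 13 | 13/140 | 17 |
| 2 | 51/102 | 10 | 38/114 | 11 |
| 3 | 76/76 | 10 | 64/89 | 10 |
| 4 | 102/51 | 10 | 89/64 | 10 |
| 5 | 127/25 | 13 | 114/38 | 11 |
| 6 | 149/3 | 33 | 140/13 | 17 |

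**Step 3: what a stratified draw could reach.** At 80 RDT-negative spots per arm the half-width is 9.3 points. The smaller arm has enough collected spots at month 4 or 20 (2,334 × 1/6 × 0.763 ≈ 297) and in B rounds 1 and 6 (2,334 × 1/12 × 0.763 ≈ 148). At month 23.5 it does not: 2,334 × 0.0208 × 0.763 ≈ 37. With 80 against 37 the half-width is 11.7 points.

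**Step 4: pooled over rounds.** With round effects fixed, the within-round information is the sum of n₁n₀/(n₁ + n₀).

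- A: random draw 151.5; stratified 5 × 40 + 25.3 = 225.3; ratio of standard errors √(225.3/151.5) = 1.22.
- B: random draw 154.7; stratified 6 × 40 = 240; ratio √(240/154.7) = 1.25.

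Counting whole clusters at each survey gives 1.23 and 1.24. The pooled half-width, 1.96·√(0.09/information), is about 4.7–4.8 points for the random draw and 3.8–3.9 for the stratified draw.

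**Step 5: clustering.** A generalised least squares calculation on 81 clusters × 6 rounds, with fixed round effects and a cluster intercept, gives ratios of about 1.15–1.16 at an intracluster correlation of 0.05 and 1.11–1.12 at 0.10. Moving part of the correlation to cluster-by-round level changes these by one or two points, so the range is about 11–17%.

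**Step 6: source of the gain.** Replacing 153 by 160 RDT-negative spots gives only √(160/152.6) = 1.024. In B, balancing the same 153 between arms gives √(6 × 38.15/154.7) = 1.216, and 1.216 × 1.024 = 1.245. Balance does nearly all the work.

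**The case against.** Several points on the other side stand.

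- **No bias.** A random sample estimates sub-patent prevalence validly. Only precision is at issue.
- **Rounds are pooled.** The analytical plan uses mixed models, and no round-by-round sub-patent contrast is planned. Over the six rollout rounds in B the random draw gives 600 spots in each arm. A reader might infer from step 2 that the arm comparison cannot be made; the documents do not support that. Even single rounds in mid-rollout have 38 or more informative spots in the smaller arm.
- **RDT-positive spots are not wasted.** A reader might infer that a quarter of the PCR tests are thrown away. The stated purpose is RDT validation, which needs them, and the remedy itself keeps 40.
- **The 33-point figure is fragile.** It rests on an assumed survey at month 23.5; under B the worst round is 17 points.
- **Uneven arms are inherent in a stepped wedge**, and rounds with only one arm still serve the comparison with baseline. One baseline and one full-coverage round give about 153 against 153, a half-width of 1.96·√(0.09 × 2/152.6) = 6.7 points.
- **The spots available may be fewer.** The power section works with a minimum of 907 persons. At that yield the smaller arm has about 14 RDT-negative spots at month 23.5 (907 × 0.0208 × 0.763) and about 58 in B rounds 1 and 6. The ratios without clustering fall to √(212.2/151.5) = 1.18 and √(227.0/154.7) = 1.21.
- **The article is condensed.** It says only that the sample was random; a fuller protocol may describe stratification.

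None of this removes the mismatch. The article itself fixes the number and selection of the spots and assigns PCR to a between-arm outcome. The pooled ratios in steps 4 and 5 already allow for the unevenness that pooling can recover.

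**Conclusion.** The point holds as a moderate, avoidable loss of precision on part of a secondary objective. For the contemporaneous arm contrast, the random draw's standard error is about 23–24% larger than that of a stratified draw of the same size if clustering is ignored, and about 11–17% larger at an intracluster correlation of 0.05–0.10. This rests on linear rollout, two assumed survey calendars, an assumed 10% sub-patent prevalence, the baseline RDT prevalence holding throughout, a full 10% survey yield, and round effects treated as fixed. It does not affect the primary outcome, RDT prevalence or the validity of the sub-patent estimate. It is worth changing because the remedy needs no extra tests.

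**What to change.** In survey rounds where both arms exist, keep 200 PCR tests but draw them at random within arm and RDT result: for example about 80 RDT-negative and 20 RDT-positive spots per arm, or all available where an arm has fewer. Keep the simple random draw before rollout and after full coverage, where there is only one arm to sample.

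Estimate sub-patent prevalence among RDT-negative people directly within each arm. For prevalence among all residents, multiply by the arm's RDT-negative share from the full survey. Weight by the known sampling fractions when reporting island-wide RDT accuracy.

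The cost is a changed sampling list, sampling weights, and slightly less precise island-wide RDT accuracy.

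The article reports that rollout was already complete at submission. If the PCR is also finished, test remaining spots from the smaller arm in the early and late rollout rounds, provided they were kept; this adds tests. Otherwise state that the sub-patent arm comparison is descriptive. If the draw was in fact stratified, say so.
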